### Recruitment

The recruitment will occur in the School of Dentistry, as it receives a considerable number of patients looking for dental treatment. An average of 200 patients seeks dental treatment attendance per month, totaling approximately 2400 patients per year. The patients will be aleatorily selected from this broader sample.

### Assignment of interventions

#### Allocation: sequence generation and concealment mechanism

The random list will be generated via the website (www.sealedenvelope.com). The study participants will be examined, classified according to predetermined criteria determined by the randomization stratified by blocks, and then referred to the examiner to evaluate the restorations. The strata will be: (1) DMF-T index less or equal to 4 without caries activity; (2) DMF-T index less or equal to 4 with caries activity; (3) DMF-T greater than 4 without caries activity; and (4) DMF-T greater than 4 with caries activity.

To ensure allocation confidentiality, we will use opaque, sealed, and consecutively numbered envelopes. The allocated group will be revealed to the examiner before the start of the examination.

### Implementation

A clinical operator not involved with the study design or evaluation will carry out the patient's initial exam. A pre-calibrated examiner will then examine the restorations and indicate the treatments based on the criteria defined by the randomization. The responsible for the dental treatment will perform the treatments based on the patient’s treatment plan provided for them, without any access to the allocation group of the patient.

### Blinding

The patients, care providers responsible for the dental treatment (undergraduate students and graduate students), and the assessor who will evaluate the outcomes will be blind to the participants’ allocation group.

### Data collection, management, and analysis

The follow-up assessments will be performed by a pre-calibrated examiner, who does not have previous contact with the patient and with last information about the allocation groups and treatments performed. The treatment needs will be established according to the demands of the patients.

The clinical data will be registered on sheets previously organized on Microsoft Excel Software. All data, except those that might reveal the participants’ identities, will be shared in a public repository after accepting all manuscripts related to these studies.

The survival analysis will be used to analyze the primary outcome. Kaplan–Meyer graphs will be constructed, and the methods will be compared to each other with Cox regression with shared frailty. The calculation of sensitivity, specificity, and accuracy will consider the results obtained with the indices and the classification of the presence or not of caries lesion by the proposed reference standard. 95% CI values will be calculated with adjustments as one individual may have more than one restoration included, using a suggestion previously published [19]. The sensitivity, specificity, and accuracy between the methods will be compared using multilevel analysis (3 levels: assessment, tooth, and child/adults). As also, for the comparisons between the treatment decisions obtained with the different criteria. The cost-effectiveness ratio will also be verified, considering as effect the prevention of the primary outcome, as well as other secondary endpoints of interest, and the cost spent to reach such a condition with each of the indices. For all tests, two-tailed analyzes will be used, considering a level of significance of 5%. Analyzes will be performed using the statistical package Stata 15.0 (Stata Corp, College Station, USA).

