#### Interventions

Firstly, all patients’ dental surfaces will be examined according to the International Caries Detection and Assessment System (ICDAS) [13]. Patients meeting the inclusion criteria will be classified into subgroups. The individuals will be classified according to caries experience using the Decayed, Missing, Filled permanent Teeth (DMF-T) in 2 groups: index less or equal to 4, or index greater than 4; and also, according to the caries activity (with or without caries activity), for later block stratification.

In this first appointment, a questionnaire will be applied to assess the impact of oral health on adults’ quality of life. The instrument used will be the validated Brazilian version of the Oral Health Impact Profile-14 (OHIP-14) questionnaire [15].

The participants will be allocated into two groups (Fig. 1) according to the strategy used to diagnose and determine the treatment for caries lesions around restorations.a*FDI group* Diagnosis and treatment decision based on the International Dental Federation (FDI) criteria (Fig. 2).b*Experimental group* Diagnosis and treatment decision according to Caries Associated with Restorations or Sealants (CARS) detection criteria, described in the ICCMS (Figs. 3, 4).

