### Sample size

The sample calculation was performed based on the primary outcome of the randomized clinical trial (percentage of restorations requiring reintervention). The calculation considered a 2-year failure rate of approximately 10% for occlusal restorations [16] and 30% for occlusal-proximal restorations [17]. It was also assumed that about 10% of the replaced restorations and 14% of the restorations undergoing repair fail again [18]. Thus, estimating that half of the sample is from occlusal restorations, an operative reintervention requirement rate of 24% was estimated in 2 years. The number of 522 restorations was reached, based on an absolute difference of 10% between the groups, using a two-tailed test. As a participant can contribute with more than one restoration, 20% was added to this value (n = 626). Thus, considering a predetermined average of inclusion of 5 teeth per patient, and adding 20% to possible sample losses, a minimum number of 152 patients was reached to be included in the trial.

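### Randomisation is stratified by DMF-T and caries activity, but the stated primary Cox frailty model names neither factor; if they are prognostic, some power is lost

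*Protocol article*

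**What the plan says.** Under Interventions, each patient is classified by DMF-T and by caries activity at the first examination, and the only purpose given is "for later block stratification". Under Allocation: sequence generation and concealment mechanism, patients are "classified according to predetermined criteria determined by the randomization stratified by blocks". Four strata are listed, from "The strata will be: (1) DMF-T index less or equal to 4 without caries activity" to "4) DMF-T greater than 4 with caries activity".

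Under Data collection, management, and analysis, the primary outcome is to be shown in Kaplan–Meier graphs, and "the methods will be compared to each other with Cox regression with shared frailty". Tests are two-sided at 5%. No covariate or stratum term is named for this model, and none is ruled out.

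Under Sample size, "an operative reintervention requirement rate of 24% was estimated in 2 years". The number of patients is then derived "considering a predetermined average of inclusion of 5 teeth per patient".

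**The concern.** Stratified allocation forces the arms to be alike on DMF-T group and caries activity. If these factors drive failure, the forced balance reduces the true variance of the difference between methods. A frailty model containing method alone does not see this. It absorbs the variation between strata into the patient frailty and carries it into the standard error, so the test becomes conservative and power is lost.

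The factors are plausible predictors. They are the only ones the design stratifies on, and the Background names secondary caries as the main reason restorations fail. Naming the model in advance also removes a later choice between an adjusted and an unadjusted result.

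**Working it through.** **1. The plan's own figure.** Inputs from Sample size: 24% at 2 years, absolute difference 10 points, two-tailed. Power is not stated; 80% is inferred because it reproduces the result. With 24% against 14%, mean 19%:

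- n per arm = [1.96·√(2·0.19·0.81) + 0.8416·√(0.24·0.76 + 0.14·0.86)]² / 0.10² = 240.4, so 241 (482 in total).
- With continuity correction: 261 per arm, 522 in total, as stated.
- 522 × 1.2 = 626.4, stated as 626. Then 626 / 5 = 125.2, so 126 patients; 126 × 1.2 = 151.2, so 152.

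The chain reproduces without any covariate, so the sample size never relied on adjustment.

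**2. What omitting the factors costs.** The article does not say how strongly either factor predicts failure, nor how large the strata are, so a range was simulated.

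- From the plan: 126 patients (after losses), 5 restorations each, 24 months, four strata, 24% against 14% (24% in both arms for type I error), two-sided 5%.
- Assumed: blocks of 4; caries activity in 50%; DMF-T above 4 in 50% or 90%; each factor multiplies the hazard by 1.0, 1.5, 2 or 3; residual gamma frailty variance θ of 0.3 or 1.0.
- Baseline hazards were set so that the stratum-averaged risk, 1 − (1 + θH)^(−1/θ), equals the target, where H is the cumulative hazard in the stratum.
- Analysis: the constant-hazard form of the shared-frailty Cox model, Wald test, with method alone or with method plus both factors; 4,000 runs per cell.

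Results in per cent (gap in percentage points):

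| θ | DMF-T >4 | HR per factor | Type I, method only | Type I, with factors | Power, method only | Power, with factors | Gap |
|---|---|---|---|---|---|---|---|
| 0.3 | 50 | 1.0 | 5.4 | 5.8 | 85.2 | 85.6 | 0.4 |
| 0.3 | 50 | 1.5 | 4.7 | 5.8 | 82.5 | 84.2 | 1.7 |
| 0.3 | 50 | 2 | 3.6 | 6.0 | 80.5 | 84.9 | 4.4 |
| 0.3 | 50 | 3 | 1.9 | 5.9 | 76.2 | 86.4 | 10.2 |
| 1.0 | 50 | 1.0 | 5.2 | 5.3 | 73.0 | 73.4 | 0.4 |
| 1.0 | 50 | 1.5 | 5.1 | 5.8 | 73.4 | 75.5 | 2.1 |
| 1.0 | 50 | 2 | 4.4 | 5.4 | 70.5 | 73.9 | 3.4 |
| 1.0 | 50 | 3 | 3.6 | 5.4 | 66.7 | 76.0 | 9.3 |
| 0.3 | 90 | 1.0 | 5.0 | 5.2 | 84.3 | 84.6 | 0.3 |
| 0.3 | 90 | 1.5 | 4.5 | 5.2 | 83.0 | 84.4 | 1.4 |
| 0.3 | 90 | 2 | 3.9 | 5.3 | 81.5 | 83.7 | 2.2 |
| 0.3 | 90 | 3 | 2.8 | 5.1 | 78.7 | 84.9 | 6.2 |
| 1.0 | 90 | 1.0 | 4.9 | 5.1 | 71.5 | 71.7 | 0.2 |
| 1.0 | 90 | 1.5 | 5.0 | 5.4 | 72.1 | 73.0 | 0.9 |
| 1.0 | 90 | 2 | 5.1 | 5.9 | 71.1 | 73.7 | 2.6 |
| 1.0 | 90 | 3 | 4.0 | 5.3 | 70.0 | 74.5 | 4.5 |

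The Monte Carlo standard error is about 0.35 points for type I error and 0.6 to 0.7 for power. The adjusted test ran slightly above nominal (5.1 to 6.0%), so part of each gap comes from that. Interval censoring between visits and follow-up beyond 24 months were not modelled.

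**3. The DMF-T cut.** Every included tooth is a restored permanent tooth and so adds 1 to DMF-T. A patient at the planned average of 5 therefore has DMF-T of at least 5, above the cut, before any other tooth is counted. As an illustration, take 1 + Poisson(4) included teeth (mean 5). Then P(Poisson(4) ≥ 4) = 57% exceed the cut on included teeth alone. With two further affected teeth it is P(Poisson(4) ≥ 2) = 91%. The two-level factor may then be lopsided and carry little of the information in the score.

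**The case against.** The strongest reply is that this reads much into one sentence of a condensed article. A covariate list commonly belongs to the full protocol or analysis plan, and nothing in the sentence conflicts with the allocation section. That stands to this extent: a reader might infer that the model contains method alone, and the text does not say so. What remains is that the model as stated omits the two factors the design was built on, and that naming them gives a better model from data already in hand.

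A reader might also infer that power is certainly lost. The article does not support that, since it gives neither prognostic strength nor stratum sizes. With no stratum effect nothing is lost, and at a hazard ratio of 1.5 per factor the loss is small. Nor is validity at risk, because the method-only test errs on the conservative side.

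The DMF-T argument cuts both ways. If nearly everyone is above 4, omitting the two-level factor alone costs little. Five teeth is also only an average, and Eligibility requires just one restoration, so patients at or below 4 can enrol. This limits the value of the two-level term but leaves the case for the continuous score intact.

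Finally, it is tempting to extend the point to the treatment-decision comparison or to OHIP-14. The first does not follow, because the same examiner scores each restoration by both criteria. For the second, the article states no model to criticise.

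**Conclusion.** The point holds as a matter of efficiency. The stated primary model does not name the stratification factors. If it is fitted with method alone, the assumed range gives a loss from nil (hazard ratio 1.0) through about 1 to 2 points (1.5 per factor) and 2 to 4 (2) to about 5 to 10 (3). The upper figures require both factors to be strong predictors, and all the gaps are somewhat flattered by the slightly liberal adjusted test. Type I error of the method-only model falls to 1.9 to 4.0% at a hazard ratio of 3. In no scenario does it exceed 5% by more than simulation error. The gain from continuous DMF-T was argued from the planned tooth count and was not simulated.

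**What to change.** State the primary model as Cox regression with patient-level shared frailty and terms for method, caries activity and DMF-T stratum, and enter baseline DMF-T as a continuous covariate as well. If a fuller plan already specifies this, a cross-reference is enough. Settle it before outcomes are analysed. The cost is one sentence: both variables are recorded before randomisation, no new data are needed, and the 522, 626 and 152 figures do not change.

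### The four randomisation strata are absent from the stated primary Cox model; if they predict failure and are left out, the test is conservative and some power is lost

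*Protocol article*

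**What the plan says.** In the Protocol article, the Interventions section classifies each patient by caries experience (DMF-T of 4 or less, or above 4) and by presence of caries activity. The only purpose it gives is "for later block stratification". The section on sequence generation and concealment has participants "classified according to predetermined criteria determined by the randomization stratified by blocks" and then lists the four cells: "The strata will be: (1) DMF-T index less or equal to 4 without caries activity", and so on through the other three combinations. Block size and allocation ratio are not given.

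The section on data collection, management and analysis gives the primary comparison as survival curves and then says that "the methods will be compared to each other with Cox regression with shared frailty". No covariate is named and none is ruled out. The frailty unit is not named either, although the patient is the natural reading because one patient can contribute several restorations.

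The Sample size section does not use the strata. It takes a two-year figure, "an operative reintervention requirement rate of 24% was estimated in 2 years", and a number of restorations "based on an absolute difference of 10% between the groups, using a two-tailed test".

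**The concern.** Blocking within strata forces the two arms to be nearly balanced on DMF-T group and caries activity. The treatment estimate therefore varies less from one randomisation to another than it would under simple randomisation. A model without the strata does not know this. It sees patients from high-risk strata failing more often and attributes the difference to unexplained variation between patients, that is, to the frailty variance.

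The frailty does not cure the problem. Treatment is assigned to the patient, so the frailty variance is exactly the variance charged to the treatment contrast. The reported standard error is then larger than the true sampling variability, the confidence interval for the hazard ratio is too wide, and the test rejects less often than its nominal level.

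At stake is some power in the primary comparison, not its validity. There is also a smaller matter of pre-specification: if the terms are not written down, adjusted and unadjusted models can both be defended later, with different p-values.

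**Working it through.** **1. The plan's own figure.** Take 24% against 14%, two-sided 5%, equal arms, and 80% power (the article does not state power or allocation ratio, so both are assumptions).

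n per arm = [1.96·√(2·0.19·0.81) + 0.8416·√(0.24·0.76 + 0.14·0.86)]² / 0.10² = (1.0874 + 0.4631)² / 0.01 = 240.4.

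With continuity correction: (240.4/4)·[1 + √(1 + 4/(240.4·0.10))]² = 60.1 × 4.326 = 260.02, so 261 per arm and 522 in total, as stated. Then 522 × 1.2 = 626; 626/5 = 125.2, rounded up to 126; 126 × 1.2 = 151.2, rounded up to 152. The sample size reproduces and does not depend on the strata.

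**2. Implied hazard ratio.** ln(1 − 0.14)/ln(1 − 0.24) = 0.55, so log HR = −0.5986.

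**3. Simulation inputs.** From the article: four strata, 24% two-year failure, the 10-point difference, 5 restorations per patient, 24 months. Assumed, because the article gives no values: stratum hazard ratios, stratum sizes, frailty variance and block details. Both sets fit a gamma shared-frailty proportional-hazards model with an exponential baseline, standing in for Cox, with and without stratum terms.

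- Set A: 126 patients with 5 restorations each, four equal strata, balanced allocation within stratum, frailty variance 0.5, 1,500 runs per scenario.
- Set B: 122 patients (152 × 0.8 = 121.6) with a mean of 5 restorations, blocks of 4, 50% with caries activity, 75% with DMF-T above 4, DMF-T HR 1.5, caries-activity HR 2 or 3, frailty variance 0.2, 2,500 runs per scenario. The highest-to-lowest stratum HR is 2 × 1.5 = 3 or 3 × 1.5 = 4.5.

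**4. Results.** SE is the mean model standard error and SD the empirical one, both at treatment HR 0.55 and without stratum terms. Type I error and power are given without / with stratum terms.

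| Set | Highest-to-lowest stratum HR | SE | SD | SE/SD | Type I error % | Power % |
|---|---|---|---|---|---|---|
| A | 1 | 0.230 | 0.235 | 0.98 | 5.9 / 6.3 | 74.6 / 75.6 |
| A | 2 | 0.235 | 0.233 | 1.01 | 5.1 / 5.9 | 74.5 / 76.3 |
| A | 4 | 0.250 | 0.228 | 1.10 | 3.9 / 5.7 | 69.4 / 74.3 |
| A | 8 | 0.275 | 0.245 | 1.12 | 3.1 / 5.7 | 59.1 / 70.5 |
| B | 3 | 0.226 | 0.221 | 1.02 | 4.2 / 5.8 | 74 / 78 |
| B | 4.5 | 0.238 | 0.217 | 1.10 | 3.3 / 5.5 | 71 / 78 |

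With no stratum effect, set B gives power of 77% without and 78% with the terms.

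**5. Mechanism.** In set A at treatment HR 0.55, the median estimated frailty variance without strata rises from 0.47 to 0.53, 0.73 and 1.08 as the stratum HR goes 1, 2, 4, 8. With strata it stays between 0.41 and 0.44. The mean log HR is nearly the same in both fits (−0.598 and −0.600 at stratum HR 4), so there is no bias.

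**6. How much of the power gap is the standard error?** Use power ≈ Φ[(0.5986 − 1.96·SE)/SD] for set B.

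- Stratum HR 3: Φ[(0.5986 − 1.96·0.226)/0.221] = Φ(0.704) = 75.9%. With SE = SD = 0.221: Φ(0.749) = 77.3%. The gap is 1.4 points of the 4 observed.
- Stratum HR 4.5: Φ[(0.5986 − 1.96·0.238)/0.217] = Φ(0.609) = 72.9%. With SE = SD = 0.217: Φ(0.799) = 78.8%. The gap is 5.9 points of the 7 observed.

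Some of the rest is the adjusted Wald test running slightly above 5%.

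**The case against.** The strongest reply is that the article is silent rather than explicitly unadjusted. It never says that treatment is the only term, and a covariate list is something that a condensed article may leave to an analysis plan. A reader might infer that the trial has specified an unadjusted analysis; the text does not support that. What stands is narrower: the primary model is written down, it names treatment and frailty, and fitted as written it does not reflect how patients were randomised.

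Secondly, the effect is conditional. The article gives no failure rates by stratum, no stratum sizes and no frailty variance. The Background is mixed on how prognostic caries status should be: it calls secondary caries the main reason for restoration failure, yet puts that cause at only 2–3% in controlled trials. With weakly prognostic strata, nothing of note is lost. With 2,500 runs the Monte Carlo standard error at 5% is √(0.05·0.95/2500) = 0.44 points, so the 4.2% type I error at stratum HR 3 is not clearly below nominal. The simulations also use an exponential baseline over 24 months, not Cox over follow-up to 60 months. All of this stands and limits the size, not the direction.

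Three further inferences should be resisted. The benefit of stratification is not thrown away: in set B at stratum HR 4.5 the true SD is 0.217 without strata and 0.215 with them, so the estimate keeps its precision and only the reported uncertainty is too large. The Cox model is not the analysis that the trial was sized on; that was a comparison of two proportions. And the multilevel models compare the two criteria applied to the same restorations, so patient-level strata are not the issue there.

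**Conclusion.** The point holds in conditional form. If the primary model is fitted as stated and DMF-T group and caries activity predict failure, the standard error of the treatment effect is overstated and the test is conservative. The excess is about 0 to 2% at a highest-to-lowest stratum HR of 1 to 3, with power gaps of 1 to 4 points that are partly an artefact of the slightly liberal adjusted test. It is about 10%, with 5 to 7 points of power, at an HR of 4 to 4.5. Larger losses (11 points at HR 8) need very strong stratum effects.

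These figures rest on assumed stratum effects, stratum sizes and frailty variances, 24 months of follow-up and equal allocation. The direction agrees across two different sets of assumptions. A reader might take this as a threat to the validity of the primary result or to the sample size; it is neither. There is no bias, no inflated type I error and no change to 522 restorations or 152 patients. It is a cheap improvement that should be made before outcomes are compared by group.

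**What to change.** In the section on data collection, management and analysis, replace the primary-model clause with wording such as: the two groups will be compared by Cox regression with a shared frailty at patient level, with treatment group, caries activity (present or absent) and DMF-T group (4 or less, above 4) as fixed covariates. The product of the two factors can be added so that all four cells are represented, but this should be decided in advance. If an analysis plan already contains these terms, citing it is enough.

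The cost is one sentence and two degrees of freedom, or three with the product. Both factors are recorded for every patient before allocation, so nothing new is collected. The sample size is unchanged, and the within-tooth multilevel comparisons of the two criteria need no change. The adjusted Wald test ran at 5.5 to 6.3% in the simulations, so the small-sample behaviour of the chosen test deserves a check when the model is fixed.

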### Monitoring

#### Data monitoring

Independent regulation of data collection, management, and analysis will be assumed independently by [name].

#### Harms

The procedures performed offer minimal risk to the oral health of patients. The adverse effects are represented by the teeth with pain episodes, postoperative sensitivity, tooth fracture during the restorative procedure, teeth requiring endodontic treatment, and exodontia. In dental treatment, the possibility of occurrence of these effects is usually present.

#### Auditing

The data entered will be conducted by one of the authors of the study. The data will be weekly inspected. The inconsistencies will be verified, corrected, and registered.

### Ethics and dissemination

#### 2.11.1 Research ethics approval

This study was submitted and approved by the Ethical Committee from the School of Dentistry, Federal University of Pelotas (No. CAAE: 53463316.1.0000.5318).

